## 5. Data Handling and Storage

Data will be handled in compliance with the GDPR. All participant data will be pseudonymized, ensuring that identifying information is securely stored separately from other data. The mapping between participant names and reference codes will be kept in a separate, secure location to maintain confidentiality. Data will be stored according to local regulations, with appropriate measures to protect it from unauthorized access, loss, or misuse, and will then be kept for an additional five years for future research purposes, in accordance with applicable legal and ethical guidelines. Participants will have the right to access, correct, or restrict the processing of their data, as well as the right to request the deletion of their data or samples, within 10 years after the study concludes. Cross-border data transfer agreements have been signed among partners to build a common database.

## 6. Dissemination Plan

The study will follow open science principles to ensure transparency, inclusivity, and accessibility. It will involve a variety of stakeholders and use participatory methods to minimize bias and enhance the relevance of the findings. Open science practices will be applied at every stage, including study design, data collection, and analysis. All publications and data will be made available through Gold Open Access, with anonymization when necessary. Results will be stored in trusted repositories like OpenAIRE and Zenodo to ensure reproducibility. The study will also include open peer review, preprints, regular ORCID updates, and share resources under Creative Commons licenses. Findings will be disseminated through publications, conference presentations, and reports to inform future health interventions and strategies.

## 7. Conclusions

It is estimated that with 200,000 HealthyW8 users, we will prevent 10,000 obesity cases/y. In the long run, the impact will be maximized through the adoption of the project’s proposed methodology, platform, and tools by as many EU institutions and entities as possible. This study will contribute to minimizing the impact of obesity in Europe.

## Figures and Tables

**Figure 1 jpm-15-00625-f001:**
[figure not shown]
Flow-chart of the trial design and data and sample collection.

**Table 1 jpm-15-00625-t001:** Recruitment strategies in countries participating in the HealthyW8 young adults’ trials.

Country, Partner	Number of Participants Targeted for Enrollment	Number of Participants Required for Study Conclusion	Recruitment Strategies	Coordinating Entity	Medical Principal Investigator
Bulgaria, RCNE	30	20	Using the network of the Regional Cluster North-East, word-of-mouth	RCNE	No
Germany, BIPS/DFKI	30	15	Word-of-mouth, flyer, press release, Instagram	BIPS	No
Italy	101	52	Flyers, word-of-mouth, conferences, social media, institutional website, local press	USG	A medical nutritionist involved in the screening
Netherlands	40	20	Flyers and posters, institutional website and newsletter, social media, word-of-mouth	TU/e	No
Portugal	30	15	Flyers, word-of-mouth, conferences, social media, institutional website, local press	CIAS, UC	No
Portugal	30	15	Flyers, word-of-mouth, conferences, social media, institutional website, local press	UEV	No
Spain	60	25	Flyers, word-of-mouth, conferences, social media, institutional website, local press	CITA	No
Spain	30	20	Word-of-mouth, newspaper advertisement, flyers, physicians, and other healthcare professionals.	IDISBA	Yes

Abbreviations: RCNE: Regional Cluster North-East; BIPS GmbH/Deutsches Forschungzentrum fur Kunstliche Intelligenz GmbH; CIAS, UC: Research Center for Anthropology and Health of the Universidade de Coimbra; CITA: Agro-food Technological Center of Aragon; USG: Universitá Degli Studi di Scienze Gastronomiche; TU/e: Eindhoven University of Technology; UEV: Universidade de Évora; CITA: Centro de Investigación y Tecnología Agroalimentaria de Aragón; IDISBA: Foundation of Institute of Health Research of the Balearic Islands.

**Table 2 jpm-15-00625-t002:** Features included in the intervention through the HLRS.

The Gamebus Application	Promotes healthy lifestyle behavior, such as physical activity (e.g., walking and step counting), diet (e.g., preparing healthy meals, increasing the consumption of fruits and vegetables), or social participation (e.g., participating in cultural activities). The app uses gamification techniques (e.g., earning points, unlocking levels, competing on leaderboards) to motivate engagement. Developed by the Technical University of Eindhoven, GameBus serves as a prototype health data management platform, enhancing user engagement through mobile health (mHealth) platforms [19]. It includes an REST API based on Java Spring, an open-source web app frontend (using Ionic), and a restricted interface for smartwatches. Additional information can be found at the following website: https://blog.gamebus.eu/.
The Nutrida Application and Recipes	Provides personalized weekly meal plans, tailored to preferences, budget, allergies, and caloric requirements. The meal recommendation system is based on the Active Assisted Living (AAL) project, LIFANA, and has been further developed by the Nutrida app, created by NIUM, a University of Luxembourg spin-off (Esch-sur Alzette, Luxembourg), in collaboration with the Luxembourg Institute of Science and Technology (LIST) and the European Federation of the Association of Dieticians (EFAD), which integrates regional recipes into the app. Obtained data will be stored in secure Amazon servers in Europe, subcontracted by NIUM.
Wearable Device	Participants use either the Samsung Galaxy Active 2 smartwatch or the Garmin Vivosmart 5 fitness tracker to monitor 24 h movement, step count, sleep, pulse, and heart rate. The Samsung Galaxy Activity 2 smartwatches do not collect sleep data; also, heart rate and pulse are not measured continuously, and it can collect emotional states via the experience sampling method (as well as GPS tracking). Both devices comply with General Data Protection Regulation (GDPR), ensuring data privacy. The final choice of device will depend on the study’s specific requirements, as both collect similar data.
Samsung Galaxy Watch Active 2 Experiencer or Garmin Vivosmart 5 App	Data collected through Samsung/Garmin App will be stored, ensuring compliance with GDPR and utilize FHIR (Fast Healthcare Interoperability Resources) for FAIR (Findable, Accessible, Interoperable, and Reusable) data management.
Actigraph Accelerometers	Participants will be required to wear an ActiGraph accelerometer (ActiGraph wGT3X-B; ActiGraph LLC, Pensacola, FL, USA) continuously for nine consecutive days to objectively assess their physical activity levels and sedentary behavior. This device will provide detailed data on movement patterns, energy expenditure, and sleep–wake cycles, allowing for a comprehensive analysis of participants’ activity and rest periods. To ensure data accuracy, participants will be instructed on proper device placement and usage.
Calendar Web Application	Developed by EU HealthyW8 partner VirTech (Bulgaria), this application enables the study leader to schedule local events and inform participants. The event data is securely stored on servers at LIST, Luxembourg.
REDCap (Research Electronic Data Capture), VanDerBilt University (USA)	Used for completing intervention questionnaires. Additional information can be found at the following website: https://project-redcap.org/. The event data is securely stored on servers at LIST, Luxembourg.

**Table 3 jpm-15-00625-t003:** Tools used by each participating country in the young adults’ pilot study.

Country, Partner	Bulgaria, RCNE	Germany, BIPS/DFKI	Italy, USG	Netherlands, TU/e	Portugal, UC	Portugal, UEV	Spain, CITA	Spain, IDISBA
Length of intervention (months)	3	3	1.5	1–2	3	3	3	3
Length of run-in time	6	6	6	1	2	2	2	2
Gamebus	Yes	Yes	Yes	Yes	Yes	Yes	Yes	Yes
Nutrida	Yes	Yes	Yes	Yes	Yes	Yes	Yes	Yes
Wearable	Garmin	Samsung	Garmin	Samsung	Samsung	Garmin	Garmin	Garmin
Experiencer	No	No	No	Yes	Yes	No	No	No
Accelerometer	Yes	Yes	No	No	No	Yes	No	Yes
Calendar	Yes	Yes	Yes	No	No	Yes	Yes	Yes
Questionnaires	Yes	Yes	Yes	Yes	Yes	Yes	Yes	Yes
Biological samples and measures	Yes	No	No	No	No	Yes	No	Yes

Abbreviations: RCNE: Regional Cluster North-East; BIPS/DFKI: Leibniz-Institut fur Praventionsforschung und Epidemiologia-BIPS GmbH/Deutsches Forschungzentrum fur Kunstliche Intelligenz GmbH; USG: Universitá Degli Studi di Scienze Gastronomiche; TU/e: Eindhoven University of Technology; UC: Universidade de Coimbra; UEV: Universidade de Évora; CITA: Centro de Investigación y Tecnología Agroalimentaria de Aragón; IDISBA: Fundació Institut d’Investigació Sanitària de les Illes Balears.

**Table 4 jpm-15-00625-t004:** Measures included in pilot studies of each team.

Marker Class	Marker	Bulgaria, RCNE	Germany, BIPS/DFKI	Italy, USG	Netherlands, TU/e	Portugal, UC	Portugal, UEV	Spain, CITA	Spain, IDISBA
Anthropometrics	Height, weight, BMI	Yes	No	Yes	Yes	Yes	Yes	Yes	Yes
	Waist and hip circumference and ratio	No	No	Yes	No	Yes	Yes	No	Yes
	%body fat	No	No	Yes	No	Yes	Yes	No	Yes
	Visceral fat	No	No	No	No	Yes	Yes	No	Yes
	Thigh circumference	No	No	Yes	No	Yes	Yes	No	Yes
Clinical	Heart frequency	No	No	No	No	Yes	Yes	No	Yes
	Blood pressure (systolic and diastolic)	No	No	No	No	Yes	Yes	No	Yes
PA	Accelerometer	Yes	No	No	No	Yes	Yes	No	Yes
	IPAQ	Yes	Yes	Yes	Yes	Yes	Yes	Yes	Yes
Fitness	Hand grip strength, step-up test	No	No	No	No	No	No	No	No
Dietary patterns	FFQ	Yes	Yes	Yes	No	Yes	Yes	Yes	Yes
	24 h recall	Yes	Yes	Yes	No *	Yes	Yes	Yes	Yes
	Mediterranean eating patterns (MEDAS-14) **	No	No	Yes	Yes	Yes	Yes	Yes	Yes
General questionnaires	Quality of life (WHOQOL-Bref 26 items) **	Yes	Yes	Yes	Yes	Yes	Yes	No	Yes
	UEQ+ (26 items)	Yes	Yes	No	Yes	Yes	Yes	Yes	Yes
	Depression (PHQ-9; nine items) **	Yes	Yes	Yes	No	Yes	Yes	No	Yes
	Sleeping patterns (e.g., Pittsburgh Sleep Quality Index) **	No	Yes	Yes	No	Yes	Yes	No	Yes
	Intrinsic motivation (IMI seven items), **	Yes	No	No	Yes	Yes	Yes	No	Yes
	Smoking (Fagerstrom six items) **	No	Yes	Yes	No	No	No	No	No
	Alcohol intake (Audit 10 items) **	No	Yes	Yes	No	No	No	No	No
	Personality traits (BFI-10 scale 10 items) **	Yes	No	Yes	Yes	Yes	Yes	Yes	Yes
Biomarkers, inflammation	Cytokines (adiponectin, TNF-α, IL6, IL1-β, CRP)	No	No	No	No	No	No	No	Yes
Biomarkers, oxidative stress	F2- isoprostanes, malondialdehyde, DNA/RNA breakdown products, antioxidant activity (FRAP, ABTS, MDA)	No	No	No	No	No	No	No	Yes
Biomarkers of nutrient intakes	Blood cell counts, albumin, prealbumin,	No	No	No	No	Yes	Yes	No	Yes
Glucose metabolism	HbA1c and fasting blood glucose, insulin, HOMA-IR	No	No	No	No	Yes	Yes	No	Yes
Lipid profile	Total cholesterol, HDL-C, LDL-C, triglycerides	No	No	No	No	Yes	Yes	No	Yes
Urinary markers	Uric acid, urinary creatinine, urinary sodium,	No	No	No	No	Yes	Yes	No	Yes
Saliva	Cortisol	No	No	No	No	Yes	Yes	No	Yes
HLRS	Nutrida-app: Personalized meal recommender plan (based on age, gender, PA, dietary restrictions, culinary/ cultural personal preferences and local dishes, budget…)	Yes	Yes	Yes	Yes	Yes	Yes	Yes	Yes
	GameBus: Application that promotes healthy lifestyle through games and tasks linked to Nutrida and smartwatches	Yes	Yes	Yes	Yes	Yes	Yes	Yes	Yes
	Smartwatch: To register step count, pulse, sleep quality	Yes	Yes	Yes	No	Yes	Yes	No	Yes
	Calendar function to schedule social events for the participants	Yes	Yes	Yes	No	No	No	Yes	No
	UEQ+ (26 items)	Yes	Yes	No	Yes	Yes	Yes	Yes	Yes
Open Stakeholder Platform	Health video clips, recipes, lifestyle recommendations	No	No	Yes	Yes	Yes	Yes	No	Yes

* It was performed in a separate study. ** Self-applied questionnaires.

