## Abstract

**Background:** Rising obesity rates among young adults increase long-term health risks, especially cardiometabolic conditions such as type 2 diabetes mellitus. Digital interventions can offer scalable solutions to promote and support healthy behaviors by integrating personalized diet, physical activity promotion, and behavioral support. **Objective:** To assess the feasibility, user friendliness, adherence, and satisfaction of the Healthy Lifestyle Recommender System (HLRS). Secondary outcomes will include measures of metabolic health and obesity. **Methods:** A 3-month, single-arm pilot study conducted across European countries, including Bulgaria, Germany, Italy, Netherlands, Portugal, and Spain, enrolling 351 young adults (18–25 years old, BMI 18.5–29.9 kg/m^2^). The intervention includes a mobile app for meal planning (Nutrida v.1), gamified physical activity encouragement (GameBus), and real-time monitoring via a wearable smartwatch device. Primary outcomes are adherence and engagement, measured through app usage and participant feedback; secondary outcomes include anthropometry, physical activity, dietary patterns, psychological well-being, and selected biomarkers of metabolic health. **Expected Outcomes:** Improved engagement is expected to enhance lifestyle behaviors, supporting weight management and overall well-being. Findings will guide future large-scale interventions. **Conclusions:** This study will contribute to minimizing the impact of obesity in Europe.

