## 2. Methods

### 2.1. Study Design

This study is a prospective, multi-center, single-arm, non-controlled 3-month pilot trial conducted across several European locations including Bulgaria, Germany, Italy, Netherlands, Portugal, and Spain. It is designed as a preliminary three-month intervention (pre-post design) to test the feasibility and effectiveness of a mobile health application, with the goal of laying the foundation for a future 12-month longitudinal study with an intervention group (app) and a control group (standard recommendations). The current study design will be consistent across countries, with minor adaptations to account for local contexts. NCT07011368 is the registration number for this study on ClinicalTrials.gov (https://clinicaltrials.gov/study/NCT07011368 (accessed on 8 July 2025)).

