### 2.5. Intervention

The intervention was developed collaboratively by the HealthyW8 consortium and global healthcare professionals to meet the unique needs of young adults. It offers personalized features that enable participants to tailor their dietary and physical activity choices based on preferences, budget, allergies, and physical capabilities. Central to the intervention is the HLRS, which included features shown in Table 2.

Optional access to the Open Stakeholders Platform (OSP) for supplementary information and knowledge exchange among stakeholders in obesity prevention will be found at https://www.stakeholders.healthyw8.eu/.

Table 3 provides an overview of the specific tools and equipment used in each participating country for the pilot study. All tools for data and sample collection and analysis, as well as for shipping these samples to the laboratories that will analyze them (LIH and IDISBA), were previously defined and harmonized, ensuring methodological consistency while allowing for country-specific adaptations.

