### 2.6. Follow-Up and Data Collection

The study spans 90 days (3 months) and is structured into five phases: enrollment (Dx), baseline visit (Day 0), and final visit (Day 90) in most of the participating partners. Data collection occurs at baseline and final visits, with regular check-ins via phone calls, or in-person meetings to maintain engagement. Figure 1 summarizes the timeline and interventions at each stage. Each study phase (outlined in Table 4) is described as follows:Enrollment visit (Dx): Informed consent (after receiving written and verbal information about the study’s objectives, risks, and benefits), eligibility assessment (assessed based on anthropometric measurements, and screening questionnaires on general health and lifestyle), and meeting inclusion criteria.Baseline visit (Day 0): Anthropometric data, baseline questionnaires, biological samples (blood, urine, and saliva, where applicable), and instructions on using the HLRS platform. Recommendations will be adapted to the previously diagnosed health status, A1c levels or blood pressure of the participant. Participants will receive instructions on using the HLRS platform.Final visit (Day 90): Repeat assessments and questionnaires to evaluate changes over the study.

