## 3. Statistics

Sample Size Calculation: The study hypothesizes that the use of HLRS (≥45 min per week) will not decrease by more than 20% over the 3-month intervention period. Assuming a 30% standard deviation in usage, a 0.05 significance level, and 80% power, 20 participants would be required for a paired design. To compensate for an expected 33% attrition, 30 participants will be recruited, ensuring sufficient power. An equal distribution of males and females will be targeted to enhance the generalizability of the findings.

Handling of Missing Data and Dropout: No imputation will be performed for missing data. Participants who withdraw will be excluded from further analysis beyond their last available data. In order to maintain sample size and statistical power, replacements will be made as necessary, ensuring at least 20 participants complete the study. This method safeguards the integrity of the data and minimizes potential bias.

Data Analysis: Normality of the data will be assessed through Q-Q plots and Kolmogorov–Smirnov tests. Non-normally distributed data will be analyzed using non-parametric methods such as the Friedman test, followed by pairwise comparisons, and log transformations if appropriate. A significant level of *p* < 0.05 will be considered. Data will be analyzed using SPSS (version 25.0) and R (version 4.4.1). Since outcomes will be mainly descriptive, simple and descriptive statistics will summarize baseline participant characteristics, and changes over time will be assessed using paired t-tests, to evaluate the impact of the intervention on health outcomes.

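### The text sets a 3-month intervention and a 3-month usage hypothesis, but Table 3 gives Italy 1.5 months and the Netherlands 1–2 months, together 40% of participants

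*Protocol article*

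**What the plan says.** Four places in the protocol article set the length at 3 months and name no site as an exception:

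- **Abstract, Methods:** "A 3-month, single-arm pilot study conducted across European countries, including Bulgaria, Germany, Italy, Netherlands, Portugal, and Spain". Italy and the Netherlands are both named.
- **Section 2.1:** a 3-month pilot trial, with the statement "The current study design will be consistent across countries, with minor adaptations to account for local contexts".
- **Section 2.6:** "The study spans 90 days (3 months", and the closing assessment is defined as "Final visit (Day 90): Repeat assessments and questionnaires to evaluate changes over the study".
- **Section 3, sample size:** use of the system "will not decrease by more than 20% over the 3-month intervention period".

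Table 3, in the row headed "Length of intervention (months", gives 3 for Bulgaria, Germany, both Portuguese sites and both Spanish sites, 1.5 for Italy, and 1–2 for the Netherlands.

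Two other phrases allow for some variation between sites. Section 2.5 describes the tools for data and sample collection as "ensuring methodological consistency while allowing for country-specific adaptations", and section 2.6 places the "final visit (Day 90) in most of the participating partners".

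**The concern.** The usage hypothesis is about change over 3 months of intervention. A participant who receives 1, 1.5 or 2 months of intervention has no value for that quantity. This holds whether sites are pooled or analysed one by one: pooled, about 40% of participants cannot contribute a 3-month value; site by site, Italy and the Netherlands cannot address the hypothesis at all.

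For the secondary pre-post measures that these two sites collect, such as weight and BMI, change at these sites reflects one third to two thirds of the stated exposure. Someone who follows the text alone would label those results as 3-month or Day 90 results. The Dutch range adds a second problem, because exposure is not fixed even within that site.

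**Working it through.** **1. The plan's own sample size.** Inputs from section 3: a fall of 20%, SD 30%, significance level 0.05, power 80%, paired design. Two-sided, by normal approximation:

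n = ((1.960 + 0.842) × 30/20)² = 17.66, so 18.

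The exact paired t calculation gives n = 20 with power 80.7%, which reproduces the stated 20. With 33% attrition, 20/(1 − 0.33) = 29.9, so 30, as stated. The arithmetic is sound; the difficulty is the time horizon attached to it.

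**2. Participants at the two shorter sites (Table 1).**

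| | Targeted | Required to conclude |
|---|---|---|
| Italy | 101 | 52 |
| Netherlands | 40 | 20 |
| Both | 141 | 72 |
| All eight sites | 351 | 182 |
| Share of the two | 40.2% | 39.6% |
| Six 3-month sites | 210 | 110 |

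Totals: 30 + 30 + 101 + 40 + 30 + 30 + 60 + 30 = 351, and 20 + 15 + 52 + 20 + 15 + 15 + 25 + 20 = 182. Italy is the largest site.

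**3. Exposure relative to the text.** Italy: 1.5/3 = one half. Netherlands: 1/3 to 2/3.

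**4. Does the run-in close the gap?** Table 3 lists a run-in of 6 for Italy and 1 for the Netherlands, without a unit. If the unit is weeks (an assumption), Italy has about 1.4 + 1.5 = 2.9 months in all, but the Netherlands has only about 0.2 + (1 to 2) = 1.2 to 2.2 months. If the unit is months, the Netherlands reaches 2 to 3 months and Italy 7.5. Neither reading brings both sites to 3 months, and the other six sites have 3 months of intervention besides their run-in.

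**5. Precision if 3-month results rest on the six sites.** Half-width of the 95% CI = t(0.975, n − 1) × SD/√n, with SD 30% from section 3:

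- n = 182: 1.973 × 30/√182 = 4.4 points
- n = 110: 1.982 × 30/√110 = 5.7 points

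For weight and BMI, Table 4 shows every site except Germany collecting them, so all sites give 182 − 15 = 167 required completers and the 3-month sites give 167 − 52 − 20 = 95. Ratio of CI widths at equal SD: (1.986/√95)/(1.974/√167) = 1.33.

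The comparisons with 182 and 167 apply only if sites would otherwise be pooled, which the article does not state.

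**The case against.** The best defence is that the difference is disclosed. Table 3 prints the lengths, section 2.5 refers the reader to that table, and section 2.6 limits the Day 90 schedule to most partners. The study is a single-arm pilot with mainly descriptive outcomes, and how shorter sites enter the analysis may be settled in a fuller plan.

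Part of this stands. The shorter lengths are not hidden, and the six remaining sites can carry the 3-month question. But the wording about most partners names no site and gives no other end time, and it does not reach the abstract, section 2.1 or section 3. The phrase in section 2.5 concerns tools for collecting data and samples, not the length of the intervention. Cutting exposure to between one third and two thirds for 40% of participants is hard to call a minor adaptation. The conflict is between a printed table and printed text, so it is not a detail deferred to another document.

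Three stronger readings go further than the article supports:

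- A reader might infer that the 3-month hypothesis fails altogether. It does not; it cannot be tested at two of eight sites.
- A reader might take it as shown that Italy's final visit falls before Day 90. That is an inference: the run-in has no unit, and the article does not say whether Day 0 comes before or after it. What is shown is the shorter intervention.
- A reader might claim that the decline in use will be understated by a given amount. That would need pooling across sites and a shape for usage over time, and the article states neither.

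**Conclusion.** The text and Table 3 contradict each other on the length of the intervention at two sites with 141 of 351 targeted participants (40.2%) and 72 of 182 required completers (39.6%). A 3-month change in use under the intervention cannot be observed there, pre-post changes there follow a shorter exposure, and the Dutch length is not fixed.

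This should be corrected, but the damage is contained. The six 3-month sites together require 110 completers against the 20 calculated, and outcomes are mainly descriptive. Measures that neither site collects, such as blood pressure, glucose and lipids (Table 4), are untouched.

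The conclusion rests on reading Table 3 as printed and on taking Table 1's required completers as the number available. The figure of 110 is for the six sites combined.

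**What to change.** - State each site's intervention length and final-visit time in sections 2.1, 2.6 and 3, with a reference to Table 3, and qualify the 3-month description in the abstract. For the Netherlands, set one fixed length or record each participant's actual length.
- Give the run-in a unit and place Day 0 relative to it.
- Base the 3-month usage hypothesis, and any result labelled 3-month or Day 90, on the six 3-month sites (210 targeted, 110 required completers).
- Report Italy and the Netherlands by actual exposure.

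The cost is wording, a separate report for two sites from data already scheduled, and some precision in 3-month results. If sites would otherwise be pooled, the usage half-width rises from 4.4 to 5.7 points, still well inside the 20% margin, and 3-month change in weight and BMI rests on 95 rather than 167 required completers, with an interval about 1.33 times as wide.
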